### Randomization

After written informed consent is obtained, patients eligible for the study are randomly allocated to either group A, B, or C using a permuted block randomization scheme generated by an external statistician not involved in the study. We use a block randomization with variable block length. The varied block sizes were chosen to prevent predictability in treatment allocation. A clinician not involved in this trial keeps the randomization list and, when called, announces the intervention group to which the participant has been assigned.

### Blinding

This is an open-label study. Analysts who evaluate the primary endpoint are blinded for clinical data and interventional allocation. Hand therapists are blinded for patient-reported and disease-related data.

### Conservative interventions

*Group A: Multimodal Hand Therapy as introduced by Kaltenborn and exercise at home* [39, 40].

Over a period of 9 weeks, MHT is applied twice per week to the first carpometacarpal joint on the symptomatic side or bilaterally for 20 minutes or 40 minutes, respectively per session. The therapy is conducted by an experienced hand therapist.

In all cases, the therapy session is performed as follows:
*Manual therapy:* Transverse friction massage of the thenar muscles with moderate intensity applied two times followed by a 1-minute rest period.*Manual muscle release:* Repetitive dorsal stretching of the thenar muscles for 3 minutes followed by a 1-minute rest period.*Manual therapy*: Traction technique for grade II and III pain relief three times for 1 minute, followed by a 1-minute rest.*Strengthening exercise:* The carpometacarpal 1 (CMC-1) joint is in palmar abduction, the metacarpophalangeal 1 (MCP-1) and interphalangeal (IP) joints in flexion. The patient is asked to sustain this position of thumb opposition to the index fingertip of the same hand. The patient is asked to repetitively extend the index finger by maintaining the position of the thumb and bring the index finger back in opposition, meeting the tip of the thumb three times for 1 minute, each time followed by a 1-minute rest period.*Strengthening exercise:* The CMC-1 joint is in radial abduction and moderate extension and the patient is asked to sustain that position. Next, alternate abduction and adduction of the index finger is performed for strengthening the first dorsal interosseous muscle by moving an elastic band for 2 minutes.*Home strengthening exercise:* All participants must additionally perform a daily home exercise program. The two exercises are explained and an exercise pictogram is provided. The exercises are identical to paragraphs number 4 and 5 above.

*Group B: Application of non-pulsed and pulsed therapeutic ultrasound.*

Over a period of 9 weeks, TUS is applied to each affected CMC 1 joint for 10 minutes twice per week. There are 18 therapeutic units per affected hand in total. The patient sits in front of the assessment table; forearm and hand lie in dorsal position on the table. For the first 5 minutes, TUS is applied with a hand-held transducer in a continuous (non-pulsed) wave mode with an intensity of 1 W/cm^2^. Immediately after this procedure, the same hand-held transducer is used to apply the pulsed wave ultrasound with an intensity of 0.3 W/cm^2^ at a pulse repetition frequency of 100 Hz, and a duty cycle of 20% (ratio 1:5) for 5 minutes. Both modes (pulsed and non-pulsed ultrasound) deliver ultrasonic energy at a frequency of 2.4 MHz. Due to likely enhanced positive effects of pulsed TUS [35], a subgroup of 15 randomly assigned patients from group B receive pulsed TUS for 10 minutes and do not receive continuous TUS. Thus, the same transducer will be used and ultrasonic energy at a frequency of 2.4 MHz, average temporal intensity of 0.3 W/cm^2^ at a pulse repetition frequency of 100 Hz, and a duty cycle of 20% (ratio 1:5). All TUS treatments are conducted by experienced hand therapists and the transducer is applied with coupling gel and moved in circular motion over the CMC 1 joint. The operator, the device, the contact gel, and the position of the patients are the same at all visits. We use the ultrasound device Modell Soleo Sono (Zimmer MedizinSysteme GmbH, Neu-Ulm, Germany) and the ultrasonic transducer US S SD/SL, diameter 13 mm (1cm^2^) and an effective radiating area (ERA) of 0.65cm^2^ at 2.4 MHz.

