
## Methods

### Study design

This is a single-center, randomized, controlled, repeated-measures, three-armed, parallel-group study conducted at the Waldfriede Hospital Berlin. Recruitment started in October 2019 (ClinicalTrials.gov identifier: NCT04115085). Patients are recruited from our hand surgery outpatient clinic on the Waldfriede Hospital campus. Further recruitment strategies include specific study calls on the website of the Waldfriede Hospital and information events and lectures for patients including distribution of study flyers. We intend to randomize 150 OAT patients to one of three hand therapeutic interventions. Intervention groups are (A) MHT with 18 sessions over 9 weeks, and (B) therapeutic TUS with 18 sessions over 9 weeks, and (C) combination therapy with MHT directly followed by TUS with 18 sessions over 9 weeks. Participants are studied on the first day before the intervention starts and at 9, 13, 17 and 33 weeks after the start of the intervention. The institutional review board of Waldfriede Hospital Berlin gave a positive evaluation for the study and written informed consent was obtained from all participants prior to study entry (Additional files 1 and 2). The study is conducted in accordance with the Declaration of Helsinki in its currently applicable version, the guidelines of the International Conference on Harmonization of Good Clinical Practice (ICH-GCP) and applicable German laws. Table 1 and Fig. 1 show the visit schedule and the study flow chart, respectively. Participants do not receive remuneration. For further details refer to the SPIRIT checklist (Additional file 2).

**Table 1 Tab1:** SPIRIT SUR study schedule

Visit	-1 Screening	0 Baseline Start intervention	1 End of intervention	2 Follow-Up	3 Follow-Up	4 Final follow-up visit
Week	−12 (max)	1	9	13	17	33
Informed consent	x					
Demographics	x					
Inclusion / exclusion criteria	x	x	x	x	x	x
Case history	x					
Medication	x	x	x	x	x	x
DASH		x	x	x	x	x
SF-36		x	x	x	x	x
VAS pain		x	x	x	x	x
Key pinch force		x	x	x	x	x
Goniometry		x	x	x	x	x
MHT		x	x			
TUS		x	x			
MHT + TUS		x	x			
Physical examination	x				x	
AE / SAE query		x	x	x	x	x

*AE* adverse event, *DASH* Disabilities of the Arm, Shoulder, and Hand, *MHT* multimodal hand therapy, *SAE* serious adverse event, *SF-36* Short Form 36, *SPIRIT* Standard Protocol Items: Recommendations for Interventional Trials, *SUR* Study of Medical Ultrasound for Rhizarthrosis, *TUS* therapeutic ultrasound, *VAS* visual analogue scale

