#### Complete list of exclusion criteria

History of surgery on the affected hand, wrist, or forearmPlanned surgery within the next 8 monthsAnticoagulation (Vitamin-K antagonists, heparin)Hemophilia, von Willebrand-Jürgens syndrome, thrombocytopathy, or other blood anomaliesAcute pain medication (< 7 days)Systemic medication with corticoids or immunosuppressantsIntra-articular injections or Radiosynoviorthesis (radiosynovectomy) (RSO) within the last 3 monthsPregnancy, lactationSignificant cognitive impairmentClinically relevant or progressive systemic disease (e.g., liver, kidney, cardiovascular system, respiratory tract, vascular system, brain, metabolism, thyroid) that could affect the course of the studyMalignant diseaseSimultaneous participation in an interventional study or participation in an interventional study in the last 2 months before study inclusionClinically relevant addiction or substance abuse disorder (defined as alcohol or drug abuse)Insufficient mental capacity to cooperateSuspected lack of complianceMedical, psychiatric or other conditions that restrict the patient’s following abilities: to interpret the study information, to give informed consent, to adhere to the rules of the protocol, or to complete the study

Discontinuation criteria are withdrawal of consent, subsequent occurrence of an exclusion criterion, lack of compliance, and medical reasons for stopping the intervention. Participants meeting a discontinuation criterion are offered the chance to attend the remaining study visits for follow-up outside the study protocol.

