### Power calculation

Since this study is planned as a pilot study, formal statistical power calculations are not performed for all measures and tests of interest. The primary limitation for making power calculations is the lack of available information on what would constitute a clinically significant effect size for the measures of interest in OAT. Thus, we refer to other studies (regarding osteoarthritis of the knee and ultrasound therapy) for a “sample size calculation” since there is no justification with regard to statistical power [34, 35, 44]. The parameters determined with this pilot study will be used to plan the number of cases in a subsequent controlled prospective randomized trial. However, we estimated a sample size of 45 patients per group and defined a two-sided significance level of 0.05 for all tests. We expect a dropout rate of approximately 10% and therefore plan to enroll 50 patients per group, or a total of 150 patients.

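### Unsupervised daily home exercise is a large share of hand therapy and bears on who is analysed, but the article describes no record of it

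*Protocol article*

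**What the plan says.** Under Conservative interventions, Group A, each supervised hand-therapy session is given "on the symptomatic side or bilaterally for 20 minutes or 40 minutes, respectively per session". The same list ends with an unsupervised component: "All participants must additionally perform a daily home exercise program". On its content it says: "The exercises are identical to paragraphs number 4 and 5 above". No number of weeks is given for it.

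Study design sets arm A as "MHT with 18 sessions over 9 weeks" and arm C as "combination therapy with MHT directly followed by TUS with 18 sessions over 9 weeks". The home programme is not restated for arm C; it follows from the inclusion of hand therapy. The Group B text describes no home component.

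After the exclusion list comes: "Discontinuation criteria are withdrawal of consent, subsequent occurrence of an exclusion criterion, lack of compliance, and medical reasons for stopping the intervention". The exclusion list itself includes a mere suspicion of poor compliance, and Table 1 rechecks the eligibility criteria at every visit to week 33. Data analysis restricts the statistical analysis to patients who complete as the protocol requires. Blinding states that the trial is open-label. Table 1 has rows for hand therapy, ultrasound and the combination, marked at weeks 1 and 9, and no row for home exercise. Power calculation says: "The parameters determined with this pilot study will be used to plan the number of cases in a subsequent controlled prospective randomized trial".

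**The concern.** Three provisions meet here: a mandatory component that nobody on the study team observes, a removal rule that turns on compliance, and an analysis set limited to protocol completers. The article gives neither a measure of home exercise nor a threshold. Followed as written, someone who knows the allocation forms an impression of whether a patient exercised at home, and that impression can help decide whether the patient is analysed. Because the component exists only where hand therapy is given, this route to removal is specific to arms A and C. Removal after randomisation on an unmeasured, arm-specific judgement weakens the comparison that randomisation was meant to protect.

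There is also a loss of information. If hand therapy did no better than ultrasound, or the combination no better than ultrasound alone, home-exercise data would help to separate a treatment that does not work from exercises that were not done. Home adherence is also a useful planning figure for the trial that this pilot is meant to inform.

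**Working it through.** **The plan's own figures.** Two sessions a week for 9 weeks give 2 × 9 = 18 sessions, as stated. The enrolment target follows from 45 / (1 − 0.10) = 50 per group and 3 × 50 = 150, as stated; this point does not affect it. The listed parts of a session sum to 17 minutes plus massage if traction has one rest (1 + 4 + 4 + 6 + 2), or 19 plus massage if it has three (1 + 4 + 6 + 6 + 2). Either fits a 20-minute session, with 3 or 1 minutes of massage. The article states no share for home exercise, so there is none to reproduce.

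**Inputs for the share.**
- Exercise 4 is done "three times for 1 minute, each time followed by a 1-minute rest period": 3 × (1 + 1) = 6 min, of which 3 are active.
- Exercise 5 lasts 2 min.
- One home bout is therefore 6 + 2 = 8 min, of which 5 are active.
- Assumptions: one full bout per day, for the 9 treatment weeks, so 9 × 7 = 63 days.

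**Direct reading, one hand.** Home: 8 × 63 = 504 min. Supervised: 18 × 20 = 360 min. Share: 504 / (504 + 360) = 504 / 864 = 58.3%.

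**Other readings within 9 weeks.**

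| Reading | Calculation | Home share |
|---|---|---|
| Active minutes on both sides, massage 1 to 3 min | 315 / (315 + 216) to 315 / (315 + 252) | 59.3% to 55.6% |
| Home exercise only on the 63 − 18 = 45 non-session days | 360 / (360 + 360) | 50.0% |
| Home minutes without rests, full 20-min sessions | 315 / (315 + 360) | 46.7% |
| Both hands treated, exercised together at home | 504 / (504 + 720) | 41.2% |
| Both hands treated, exercised one after the other | 1008 / (1008 + 720) | 58.3% |
| Arm C, all treatment time (ultrasound 18 × 10 = 180 min added) | 504 / (504 + 360 + 180) | 48.3% |

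These change one assumption at a time. Stacking two unfavourable ones (45 days, and no home rests against full sessions) gives 225 / 585 = 38.5%.

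**By count of strengthening bouts.** 63 / (63 + 18) = 78% are at home, or 45 / (45 + 18) = 71% if session days are excluded.

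**The provisions side by side.** Home exercise is mandatory and unobserved (Conservative interventions). Poor compliance can end participation (discontinuation criteria). Only protocol completers are analysed (Data analysis). No section says how home compliance is known or how much is enough.

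**The case against.** The strongest objection is that this argues from silence. The article condenses a fuller protocol, Data management refers to source documents and case report forms without listing their fields, and a diary may exist. That stands as far as the record goes, so nothing here shows that home exercise is not recorded. It does not dispose of the point, because the article itself fixes compliance as a ground for removal and limits the analysis to completers.

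Three stronger readings are tempting, and the documents do not support them.
- A reader might infer from Table 1 that session attendance is not recorded either. The table's columns are assessment visits, most of the 18 sessions fall between them, and it does not list everything collected: X-ray stage and randomisation are absent. Therapists deliver every session, so attendance may well be in source documents.
- A reader might infer that compliance removals cannot fall on arm B. They can: the criterion covers all participants, and arm B has 18 sessions that can be missed. Arms A and C have one further component on which to be judged.
- A reader might take daily exercise and protocol completion together to mean that every single home day must be done, so that almost nobody would qualify. The article states no such threshold.

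Two further objections stand in part. Clock time is not therapeutic weight: 3 of the 8 daily minutes are rest, and massage, stretching and traction are supervised only. And pilot estimates already reflect whatever adherence occurred, so a comparison of therapies as prescribed can be read without a diary. However, with a completers-only analysis they reflect the adherence of a selected group, and the level stays unknown.

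**Conclusion.** The point holds for home exercise. A mandatory, unobserved component that is specific to the hand-therapy arms can influence discontinuation and the analysis set, and the article gives no measure of it. On the direct reading it is about 58% of prescribed hand-therapy time for one hand. The range is about 41% to 59% when one assumption is varied at a time, and the share is about 48% of all treatment time in arm C.

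This rests on the home programme lasting the 9 treatment weeks at one full bout a day, on its applying in arm C by implication, and on its not applying in arm B. The quoted sentence speaks of all participants, but it stands in the Group A description, whose title names home exercise. If it were meant for arm B as well, the arm asymmetry would go, and the lack of a measure would remain. Even at the low end the component is substantial, so the conclusion does not depend on its being more than half.

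How many patients would be removed, and in which direction the comparison would move, cannot be calculated from the article. No sample-size or error-rate figure changes.

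**What to change.** Unless the full protocol already provides it:
- Print a daily tick sheet on the exercise pictogram that patients already receive. Collect it at the sessions and at week 9 in arms A and C, and add a row for it to Table 1.
- Report home-exercise days for arms A and C, together with sessions attended in every arm from existing records, as a descriptive pilot result.
- State how many weeks the home programme lasts and whether it applies in arm C.
- Reconcile the discontinuation criteria, Conservative interventions and Data analysis on how compliance is judged. The clinical rule itself is for the investigators to set.
- In the analysis, keep patients with incomplete home exercise in the group to which they were randomised.

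The cost is one sheet, a case report form field and a short amendment, with no extra visit. Self-report tends to overstate adherence, the sheet may itself encourage exercise, and it covers only patients not yet treated. The sheet alone does not repair the completers-only analysis; the last item is needed for that.

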### Adverse events

Patients will be asked about the tolerability of the interventions and any adverse events (AEs) will be recorded. We do not expect serious adverse events (SAEs)due to our non-invasive and harmless interventions. There is no anticipated harm for trial participation and thus no provisions for post-trial care or compensation.

### Outcome parameters

Primary outcome is the change in the disease-specific Disabilities of the Arm, Shoulder, and Hand (DASH) questionnaire score after 9, 13, 17, and 33 weeks compared to baseline [41, 42].

Secondary patient-reported outcomes include: (1) VAS pain determined by change in distance between the patient-made mark after 9, 13, 17, and 33 weeks compared to baseline; (2) Short Form 36 (SF-36) determined by scale score change after 9, 13, 17, and 33 weeks compared to baseline [43]. Secondary disease-related outcomes include: (3) Thumb force or key pinch force evaluation, determined by change in Kg after 9, 13, 17, and 33 weeks compared to baseline. All thumb force evaluations will be assessed in the following position: Thumb on top of the radial side of the index finger below. (4) Goniometry measurement determined by change in range of motion after 9, 13, 17, and 33 weeks compared to baseline. All goniometric evaluations assess the active range of motion (ROM) of the angle between the dorsal axis of the thumb and the index finger with a manual goniometer.

All clinical assessments will be performed by the same experienced evaluator at all time intervals, who is blinded to the treatment allocation.

For safety monitoring, patients will be asked for tolerability of the interventions and in case of AEs a medical doctor is always at our site to provide help. For a detailed overview of assessments and endpoints see Table 1.

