**Methods:**

This study is a single-center, randomized, controlled, parallel-group pilot trial. One hundred fifty patients with rhizarthrosis and current disease activity will be randomized to one of three conservative interventions over 6 months. Interventions are (1) multimodal hand therapy (2) therapeutic ultrasound, and (3) combination therapy with both hand therapy and ultrasound therapy. The primary outcome measure is the Disabilities of the Arm, Shoulder, and Hand (DASH) questionnaire score after 6 months. Secondary endpoints are changes in pain, quality of life, disability progression, and changes of hand function. Safety will also be assessed.

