### Data analysis

The data collected are described using statistical parameters. Continuous data are described with mean, standard deviation, minimum, maximum and 95% confidence intervals; for categorical data, the frequencies attained and the associated percentages are given with 95% confidence intervals.

The statistical analysis will only include the patients who complete the study in accordance with the protocol. Sub-collectives can be examined exploratively if this makes sense after the survey has been completed. In addition to the primary analysis of the comparison of patients with and without ultrasound therapy, there is a comparison of the patients between the different groups.

Group differences (MHT versus TUS versus study group with MHT + TUS) regarding the primary endpoint are analyzed with the non-parametric Kruskal-Wallis test for independent samples. After the global test, the groups are compared in pairs (Mann-Whitney tests). Secondary endpoints are evaluated according to the scaling of the data but are also always tested non-parametrically. The evaluation of intra-group differences (DASH or other characteristics after 9, 13, 17, and 33 weeks) is carried out by means of a nonparametric analysis of variance for repeated observations (Friedman test). In line with the nature of the pilot study, no adjustment is made for multiple testing. A *p* < 0.05 is considered (in the exploratory sense) to be statistically significant. Missing values will be replaced using multiple imputation [45]. All occurring AEs (AEs and SAEs) are described individually.

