There are some limitations of our study design. First, a rehabilitative intervention study cannot be completely blinded. Thus, expectations and observer bias cannot be ruled out. However, we try to minimize bias by not communicating any longitudinal data during the study to patients and study personnel in contact with them. More important, the hand therapists who are implementing all of the interventions are blinded for both patient-reported and disease-related data. An additional limitation is the lack of formal power calculation due to the characteristics of an exploratory study.

One great strength of our study is that it can fill the treatment gap in osteoarthritis care, for many patients do not currently receive recommended conservative treatment before being referred for orthopedic surgery [50].

Further strengths of the study are the randomized study design, blinded outcome assessment, large sample size, long intervention of 18 treatment sessions, and 6 months of follow-up. Moreover, we focus on disease-related outcomes, but also on several patient-related outcomes, such as thumb force, thumb range of motion, pain scale and quality of life.

In conclusion, MHT and TUS are potentially safe, cost- and time-effective treatment options for OAT, and our study might close the gap between uncertainty of doctors and manual therapists about which conservative management is preferable to support their patients.

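### The primary endpoint is a single 6-month DASH score in the abstract but DASH change at four visits in the methods, and neither the deciding visit nor the deciding contrast is fixed

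*Protocol article*

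**What the plan says.** The primary outcome is stated twice in the protocol article.

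- Abstract, Methods: "The primary outcome measure is the Disabilities of the Arm, Shoulder, and Hand (DASH) questionnaire score after 6 months". This is one time point and a score.
- Methods, Outcome parameters: change in the DASH "questionnaire score after 9, 13, 17, and 33 weeks compared to baseline". This is four time points and a change.

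The Study design section places the assessments "at 9, 13, 17 and 33 weeks after the start of the intervention". The Discussion lists among the study's strengths a "long intervention of 18 treatment sessions, and 6 months of follow-up".

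The Data analysis section gives two accounts of the main comparison. One sentence begins "In addition to the primary analysis of the comparison of patients with and without ultrasound therapy" and then adds comparisons between the groups. The next paragraph says that differences between the three arms "regarding the primary endpoint are analyzed with the non-parametric Kruskal-Wallis test for independent samples", after which the arms are compared in pairs by Mann-Whitney tests. No condition on the global result is stated. The same section says that "no adjustment is made for multiple testing", gives the pilot nature of the study as the reason, and reads p<0.05 in an exploratory sense.

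**The concern.** The two definitions differ in the number of time points and in the quantity analysed. Nothing in the article says which of the four visits carries the conclusion, or how the four would be combined. A Kruskal-Wallis test for independent samples takes one value per patient, so it cannot absorb four repeated visits. It has to be run visit by visit, or on one visit that the text does not name. The contrast is open in the same way, because one test is called the primary analysis and another is assigned to the primary endpoint.

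The exploratory label does not settle this. The Introduction says the trial is meant to lead to recommendations for treatment. The Discussion hopes to show clinicians which conservative option to prefer. The Power calculation section intends to size a later trial from these results. Each use needs one identified result. Treatment is open-label and the DASH is reported by the patient, so several visits and contrasts would be available from which to pick the favourable one after the data are seen.

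**Working it through.** **The plan's own figure.** Power calculation: 45 evaluable patients per group with about 10% dropout. 45 / (1 − 0.10) = 50 per group, and 3 × 50 = 150. This reproduces. The article states no number of tests and no overall error rate, so those are derived here.

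**Does 6 months identify a visit?** Six months is about 26 weeks (6 × 4.345 = 26.07), and no visit falls there.
- Week 33 from the start: 33 × 7 / 30.44 = 7.6 months. Table 1 numbers baseline as week 1; counting 32 weeks instead gives 7.4 months.
- Week 33 from the end of intervention at week 9: (33 − 9) × 7 / 30.44 = 5.5 months, or 24 weeks.

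**Number of between-group tests on the primary endpoint.**
- Per visit: 1 (with versus without ultrasound) + 1 (Kruskal-Wallis) + 3 (pairwise) = 5.
- Over four visits: 5 × 4 = 20.
- Only the contrast labelled the primary analysis: 1 × 4 = 4.
- The within-group Friedman tests are not counted.

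**Chance of at least one p<0.05 when no arm differs.** Treating tests as independent, the formula is 1 − 0.95^k:
- k = 20: 0.64
- k = 4: 0.19

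The first figure is too high to quote, because the five tests at a visit share the same patients and visits are correlated. A simulation allows for this. Its inputs are 45 per arm (Power calculation), two-sided 0.05 for every test (same section), and with/without ultrasound taken as group A against B and C pooled. Normal data and an equal correlation between all visits are assumptions, since the article gives neither. Results from 2,000 runs per row:

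| Between-visit correlation | Any of 20 tests | Ultrasound contrast at any of 4 visits | Five tests at week 33 only |
|---|---|---|---|
| 0 | 43% | 18% | 12% |
| 0.3 | 38% | 17% | 12% |
| 0.5 | 34% | 15% | 12% |
| 0.7 | 31% | 13% | 13% |
| 0.9 | 23% | 10% | 13% |

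A larger run (20,000) gives 36.2%, 31.5% and 27.6% for any of 20 at correlations 0.5, 0.7 and 0.8. Repeated runs put the ultrasound contrast alone at about 11–16% over that range.

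**What fixing the visit and contrast does.**
- One visit and one contrast: 5%, by construction.
- Week 33, with pairwise tests read only after a significant three-group test: about 5%.
- The same, with the ultrasound contrast tested beside it ungated: about 7.5% (7.3–8.0%).

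Naming the visit alone is therefore not enough; the contrast must be named too.

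**The case against.** The strongest reply is that this is a declared pilot. The absence of adjustment is stated and justified, p-values are called exploratory, and the missing power calculation is listed as a limitation. That stands: the plan claims no control of an overall error rate, so the percentages above do not show a broken promise. They show how much room for selection an unnamed visit and contrast leave.

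Three stronger readings are tempting, and the document does not support them.

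- *Twenty primary tests.* A reader might infer this from the four visits. Only the with/without-ultrasound comparison is labelled the primary analysis, which makes four. Twenty is the upper count of between-group tests on the primary endpoint. It also assumes that each is run at every visit, whereas the Data analysis section mentions the visits only for the within-group Friedman test.
- *The primary endpoint falls at a visit that does not exist.* The Discussion describes a 9-week intervention followed by about six months of follow-up, and week 9 to week 33 is 24 weeks. The phrase most plausibly means the final visit, so this is loose labelling. The abstract does not say so, however, and even attaches six months to interventions that Study design schedules over 9 weeks.
- *The unadjusted testing is itself an error.* It is disclosed, and ordering or gating of tests may sit in an analysis plan not seen here.

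None of this removes the conflict between the abstract and the Outcome parameters section. An unseen plan cannot make the two published definitions agree.

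**Conclusion.** The point holds in a limited form. The article defines its primary outcome in two incompatible ways, gives no rule for the deciding visit, and leaves two contrasts competing for primary status. On the widest count (20 tests) the chance of at least one nominally significant result with no true difference is about 27–36%. On the narrowest (the ultrasound contrast at four visits) it is about 11–16%. Both rest on 45 per arm, normal data and an assumed between-visit correlation of 0.5 to 0.8; the wider range of 0 to 0.9 gives 23–43% and 10–18%. The contradiction in the text needs none of these assumptions. It should be settled before any outcome data are compared between arms, because a choice made later cannot be told apart from selection.

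**What to change.** 1. State one primary endpoint in the same words in the abstract and in Outcome parameters, for example: change in DASH from baseline to week 33 (24 weeks after the end of the intervention). Make weeks 9, 13 and 17 secondary, and replace 6 months by the week number.
2. In Data analysis, name one primary contrast at that visit. There are two workable options:
   - with versus without ultrasound as primary, and the three-group and pairwise tests as secondary;
   - the three-group test as primary, and the pairwise and with/without-ultrasound tests either secondary or interpreted only if the three-group test has p<0.05. The gate must cover the ultrasound contrast as well as the pairs.
3. Keep the exploratory label and the statement on multiplicity for everything that is secondary.
4. Date the change, and bring the registry entry (not seen here) into line if it differs.

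The cost is wording in three places and an amendment. Results at the earlier visits and on the other contrasts become secondary. Visits, assessments and sample size are unchanged.
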